#### Analysis of efficacy endpoint(s)

Efficacy analyses will be performed in modified intent-to-treat population (ITT) population ie, all patients with a 6-month evaluation (12-month for ovarian cohort) and at least one dose of durvalumab + tremelimumab. Analyses will be repeated in the per protocol population (patients who had received all the planned doses).

6-month PFS rate (12 month-rate in the ovarian cohort) will be determined using the Kaplan Meier method. 95% Confidence interval (CI) will be provided. Patients alive without progression will be censored.

Median follow-up will be estimated using the reverse Kaplan Meier method.

PFS and Overall survival will be estimated using the Kaplan Meier method. Six-month, 1-year, 2-year rates as well as median OS and PFS will be reported with their 95% CI.

Disease control rates at 6 months will be determined and described with its 95% binomial CI. The same method will be applied to describe the response rate after 6 months of olaparib in each cohort.

All statistical analysis will be performed with SAS 9.4. In case of comparison, tests will be two-sided.

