### Study endpoints

The primary endpoint is progression free survival (PFS) 6 months after the initiation of immunotherapy for all cohorts, with the exception of ovarian cohort evaluated at 12 months. PFS is defined as the time from the date of first dose of immunotherapy to the date of progression or death from any cause. Progression will be defined using iRECIST criteria.

Secondary endpoints are:
Disease control rate, including stable and responsive disease, evaluated 6 months after immunotherapy initiation for all cohorts except ovarian cohort, evaluated at 12 months.Overall survival (OS) evaluated at 12 and 24 months after immunotherapy initiation defined by the time of the first immunotherapy dose to the date of death from any cause.Response rate evaluated by CT scan, RECIST evaluation after 6 weeks of olaparib therapy.Olaparib toxicity evaluated at the end of STEP1 using CTCAE V5.Olaparib + immunotherapy (tremelimumab + durvalumab) toxicity evaluated at 3, 6 and 12 months after immunotherapy initiation using CTCAE V5.

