### Treatment duration and criteria for retreatment

Treatments will be administered on Day 1 for up to 4 months for olaparib + durvalumab + tremelimumab and then from day 1 of month 5 for up to day 1 of month 24 (all cohorts) or month 36 (only for ovarian cohort) for durvalumab alone or until confirmed PD, unacceptable toxicity, consent withdrawal or occurrence of events leading to treatment discontinuation (Fig. 2). Patient will have a maximum of 24 doses of durvalumab, except for ovarian cohort that will reach a maximum of 36.

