#### Sample size calculation

Sample size was determined using an A’Hern’s single stage design. The primary endpoint is progression PFS. It will be evaluated at 6 months (except for ovarian cancer with an evaluation at 18 months given the results of olaparib in SOLO-2 trial). The hypotheses are the following:
one-sided alpha risk =10%, a power = 90%,the expected rate of patients stable or in response after 6 weeks of olaparib is 80%,the expected rate of patients non-evaluable the primary endpoint is 5%,P0 and P1 are determined using hypotheses detailed above.

P0 is the highest level of inefficacy for which the new treatment will be rejected (maximal inefficacity). P1 defines the minimum required level of efficacy. The design of the trial focuses on demonstrating that this level is plausible given that the trial results and the efficacy is greater than the first proportion, P0. Taking into account these hypotheses: 270 patients will be included in the study, and at least 213 are required for statistical analyses. At the end the study, analysis of the primary endpoint will be performed on evaluable patients who were in response or stable after 8 weeks of olaparib.

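### The efficacy population requires a 6-month (ovarian 12-month) evaluation, so as written it can drop early deaths and progressions from the primary PFS analysis and bias the rate upward

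*Protocol article*

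**What the plan says.** All references are to the protocol article.

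- **Analysis of efficacy endpoint(s)** defines the modified intention-to-treat set for the efficacy analyses as "all patients with a 6-month evaluation (12-month for ovarian cohort) and at least one dose of durvalumab + tremelimumab". Both conditions must be met.
- **Study endpoints**: "The primary endpoint is progression free survival (PFS) 6 months after the initiation of immunotherapy for all cohorts", with 12 months for the ovarian cohort. On the clock and the events: "PFS is defined as the time from the date of first dose of immunotherapy to the date of progression or death from any cause".
- **Analysis of efficacy endpoint(s)**, on the estimator: "6-month PFS rate (12 month-rate in the ovarian cohort) will be determined using the Kaplan Meier method". On censoring: "Patients alive without progression will be censored".
- **Sample size calculation** describes the primary population a second time: "analysis of the primary endpoint will be performed on evaluable patients who were in response or stable after 8 weeks of olaparib". It does not define evaluable. It allows for 5% of patients being non-evaluable for the primary endpoint.
- **Analysis of efficacy endpoint(s)**, on the only repeat analysis: "Analyses will be repeated in the per protocol population (patients who had received all the planned doses". **Treatment duration and criteria for retreatment** gives the dose ceiling: "Patient will have a maximum of 24 doses of durvalumab, except for ovarian cohort that will reach a maximum of 36".
- **Follow-up**: the section on durvalumab + tremelimumab combination therapy follows all patients for progression and survival until 24 months after treatment ends. The withdrawal section asks for continued RECIST follow-up of patients who stop treatment without having progressed.

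**The concern.** Membership of the primary set depends on something that happens months after the PFS clock starts. A patient who dies in month 3 is a PFS event under the endpoint definition but cannot have a 6-month evaluation. A patient who progresses in month 2 and moves to other care need not have one, because continued RECIST follow-up after stopping treatment is spelled out only for patients who have not progressed. The patients at risk of exclusion are therefore failures, and each one removed raises the rate.

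The rule also works against the stated estimator. Kaplan-Meier censoring exists to keep patients with incomplete follow-up in the analysis, whereas this rule takes them out. Since the same set serves all efficacy analyses, the disease control rate and overall survival are affected too.

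Each cohort is compared with a fixed P0 and has no control arm in which a similar bias could cancel. An inactive regimen would have a better chance of being declared active.

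**Working it through.** **1. The plan's own figures.** The A'Hern cohort sizes cannot be reproduced, because P0, P1 and cohort sizes are not stated. Only the link between 270 included and 213 analysed can be checked:

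- 80% entering STEP 2: 270 × 0.80 = 216, close to 213.
- 80% and then 95% evaluable: 270 × 0.80 × 0.95 = 205, below 213.

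So 213 matches the number entering STEP 2. This matters below only because it leaves about three spare patients (216 − 213).

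**2. One patient under both rules.** Take death at month 3, non-ovarian cohort. Study endpoints: PFS event at month 3. Efficacy population: no 6-month evaluation, so not in the set. No sentence says that an earlier event counts as an evaluation.

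**3. Bias in the rate.** Let p be the true landmark PFS rate and f the share of failures excluded. Then

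apparent rate = p / [p + (1 − p)(1 − f)].

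With p = 0.40 (assumed):

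| Failures excluded | Share of treated patients lost | Apparent rate |
|---|---|---|
| f = 0.05/0.60 = 8.3% | 5% | 0.40/0.95 = 42.1% |
| f = 20% | 0.60 × 0.20 = 12% | 0.40/0.88 = 45.5% |
| f = 50% | 0.60 × 0.50 = 30% | 0.40/0.70 = 57.1% |

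The first row applies the plan's 5% allowance and assumes that every lost patient is a failure.

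**4. Type I error.** Assumed design: P0 40%, P1 65%, n = 29, declare activity at 16 or more successes. The exact binomial tail P(X ≥ 16) at 40% is 0.071. What happens next depends on how the smaller set is handled:

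| Handling | 5% of patients lost, all failures | 20% of failures lost | 50% of failures lost |
|---|---|---|---|
| Evaluable n held at 29 by replacement | 0.109 | 0.193 | 0.659 |
| No replacement, cut-off reset to the evaluable n | 0.096 | 0.17 | 0.54 |
| No replacement, cut-off fixed at 16 | 0.071 | 0.071 | 0.071 |

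The second row averages over the random number left evaluable, taking for each n the smallest cut-off with exact error at P0 of at most 10%. In the third row the number of successes does not change, so neither does the error. Holding n at 29 needs about 29/0.95 = 31, 29/0.88 = 33 or 29/0.70 = 41 treated patients.

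**5. Sensitivity to the assumed design.** One-sided 10%, power 90%, evaluable n held at the design size:

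| P0 / P1 (assumed) | n, cut-off | No loss | 5% of patients, all failures | 10% of failures | 25% of failures |
|---|---|---|---|---|---|
| 0.20 / 0.40 | 36, 11 | 0.089 | 0.119 | 0.141 | 0.275 |
| 0.30 / 0.50 | 39, 16 | 0.094 | 0.137 | 0.159 | 0.326 |
| 0.40 / 0.60 | 41, 21 | 0.097 | 0.153 | 0.167 | 0.352 |
| 0.50 / 0.70 | 39, 24 | 0.0998 | 0.170 | 0.170 | 0.350 |

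The no-loss column is what the fix restores.

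**6. Per-protocol set.** Suppose the planned doses are the four combination doses, the last at week 12, and patients who progress before then do not receive all four. With exponential PFS and 40% at 6 months (26 weeks), S(12 weeks) = 0.40^(12/26) = 0.655, and the rate among those retained is 0.40/0.655 = 61%. If all 24 (36) durvalumab doses are required, selection is stronger still.

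**The case against.** The best case on the other side is that the authors meant patients whose status at the landmark is known, with earlier progression or death counting as known. Three things support it:

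- The 5% non-evaluable allowance is far below the 12% or 30% of treated patients lost in the two larger scenarios.
- All patients are followed for progression and survival, so the event data would exist.
- The same section reports a six-month overall survival rate, which would be 100% by construction if everyone dying earlier were excluded.

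This makes the milder intent plausible, and it stands as a reason not to assert that exclusion will happen. It does not cure the text. The definition is affirmative, nothing in the article qualifies it, and the sample size section adds only the undefined word evaluable.

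A reader might infer three stronger conclusions that the article does not support:

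- **That the reported PFS rate will be inflated by a known amount.** The direction follows whenever a failure is excluded. How many would be is not determinable.
- **That the false-positive risk is 66%.** That needs half of all failures to be lost and each excluded patient to be replaced. The plan has almost no room for replacement, and with a fixed cut-off and no replacement the error does not move.
- **That per-protocol PFS is about 100% by construction.** The 24 and 36 doses are maxima, planned doses can be read as those due until a protocol stopping reason, and the retreatment section refers to patients treated through progression. It is also only a repeat analysis and does not drive the decision.

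Finally, counting unknown status as failure is one convention. Censoring, the article's own method, is another.

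**Conclusion.** The point holds as a defect in a stated rule. As written, the efficacy population conditions on reaching and attending a post-baseline visit that patients who die early cannot attend and early progressors may miss. This conflicts with the PFS definition and biases the landmark PFS rate, disease control rate and overall survival upward. The per-protocol repeat selects in the same direction, by an amount that depends on how planned doses is read, so it cannot serve as a check.

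The size is unknown. With an assumed true rate of 40%, the apparent rate is 42% at the plan's own 5% loss if all lost patients are failures, and 45.5% or 57% if 20% or 50% of failures are lost. Type I error rises only if excluded patients are replaced, the cut-off is reset for the smaller n, or the decision uses the estimated rate. With evaluable n held at 29 in the assumed design, it goes from 7% to 11%, 19% and 66% respectively. P0, P1, n and the loss shares are all assumptions, apart from the 5% allowance. Because the rule governs the primary decision in every cohort, it should be corrected before analysis, even if the milder meaning was intended.

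**What to change.** 1. Define the primary efficacy set as all STEP 2 patients who received at least one dose of durvalumab or tremelimumab, whether or not a landmark scan exists. Use the same definition in the sample size section in place of the undefined evaluable.
2. State that progression or death before the landmark is an event.
3. Keep patients lost without an event in the set, censored at their last assessment in the Kaplan-Meier estimate. Add a sensitivity analysis that counts them as failures in the A'Hern decision.
4. Redefine the per-protocol set by absence of major eligibility or treatment deviations, with treatment given as planned until a protocol stopping reason.

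The cost is wording in the analysis section and the analysis plan. No new data are needed. The reported rate may be slightly lower than under the present definition.

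### The efficacy population requires a 6-month (ovarian 12-month) evaluation, so as written it removes patients who die before the landmark and biases Kaplan-Meier PFS and OS upward

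*Protocol article*

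**What the plan says.** All references are to the Protocol article.

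- **Population.** Analysis of efficacy endpoint(s) names a modified intent-to-treat set consisting of "all patients with a 6-month evaluation (12-month for ovarian cohort) and at least one dose of durvalumab + tremelimumab". The two conditions are joined by *and*, so a treated patient without the landmark evaluation is outside the set.
- **Endpoint.** Study endpoints sets the primary endpoint as "progression free survival (PFS) 6 months after the initiation of immunotherapy for all cohorts, with the exception of ovarian cohort evaluated at 12 months". It adds that "PFS is defined as the time from the date of first dose of immunotherapy to the date of progression or death from any cause".
- **Estimator.** Analysis of efficacy endpoint(s) states that "6-month PFS rate (12 month-rate in the ovarian cohort) will be determined using the Kaplan Meier method" and that "Patients alive without progression will be censored". Under the same heading, "PFS and Overall survival will be estimated using the Kaplan Meier method", with rates at six months, one year and two years.
- **Repeat analysis.** The same section repeats the analyses in a per-protocol set that requires all planned doses to have been given.
- **Design.** Sample size calculation uses an A'Hern single-stage design with one-sided alpha 10% and power 90%, and says that "the expected rate of patients non-evaluable the primary endpoint is 5"%. It places the primary analysis in evaluable patients without defining that term. It gives no values for P0 or P1 and no cohort sizes.

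**The concern.** Entry to the analysis set depends on a post-treatment assessment that the outcome itself can prevent. A patient who dies in month 3 is a failure by the endpoint definition but has no month-6 evaluation, so the population rule deletes that failure. This is guarantee-time (immortal-time) selection.

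The restriction also gains nothing. Kaplan-Meier needs no landmark visit: early events enter as events, and patients lost without an event are censored.

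The trial is single-arm and each cohort is analysed separately, so no control group shares the distortion. OS is estimated under the same heading. The 12-month OS rate is a named secondary endpoint, and in the ovarian cohort the 12-month evaluation is also the entry condition. The per-protocol repeat cannot expose the problem, because it too selects patients who lasted long enough.

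**Working it through.** **1. The plan's own figures.** The 213 patients cannot be rebuilt from A'Hern, because P0, P1 and the cohort sizes are absent. Only the step to 270 can be checked: 213 / 0.80 = 266.25, close to 270. The other way, 270 × 0.80 = 216, and 216 × 0.95 = 205.2, which is below 213. The 5% therefore fits only if 213 is the number entering STEP 2, as Study population and eligibility criteria says. That arithmetic is a separate matter. Here it means that no cohort design can be recovered, so every size below rests on assumed values.

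**2. The rules applied to four kinds of treated patient.**

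| Patient | Endpoint definition | Population rule as written |
|---|---|---|
| Dies before the landmark | PFS and OS event | Excluded |
| Progresses early, no landmark evaluation | PFS event | Excluded |
| Progresses early, still evaluated at the landmark | PFS event | Included as an event |
| Lost without an event before the landmark | Censored | Excluded |

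The first two rows produce the upward bias. The first row alone makes OS at the landmark 100%.

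**3. Apparent rate.** If a share d of treated patients is excluded and all of them are failures, a true rate p appears as p / (1 − d). If instead a share q of the early failures is excluded, then d = q(1 − p) and the apparent rate is p / [p + (1 − p)(1 − q)]. With q = 0.25, a true 0.30 appears as 0.364, 0.40 as 0.471, and 0.50 as 0.571.

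**4. Kaplan-Meier simulation.** Assumed: true 6-month PFS of 0.50, non-informative loss with 10% cumulative risk by month 6, and 400,000 patients.

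- Everyone kept, leavers censored: 0.499.
- Early leavers dropped (7.2% of patients): 0.484.
- Early leavers and 25% of early failures dropped: 0.556.
- Early leavers and all early failures dropped: 1.00.

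The bias therefore comes from the excluded events, not from the excluded leavers.

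**5. False-positive rate.** Assumed design: P0 = 0.30, P1 = 0.55, 25 evaluable patients, success declared at 11 or more. Exact binomial: alpha 0.098, power 0.904. Excluded failures are assumed to be replaced, so that 25 evaluable patients are still analysed. The table gives P(X ≥ 11 | 25, P0 / (1 − d)).

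| d | Apparent rate under P0 | P(X ≥ 11) |
|---|---|---|
| 0 | 0.300 | 0.098 |
| 5% | 0.30 / 0.95 = 0.316 | 0.132 |
| 10% | 0.30 / 0.90 = 0.333 | 0.178 |
| 20% | 0.30 / 0.80 = 0.375 | 0.317 |

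The 5% row borrows the article's non-evaluable rate and takes all of those patients as failures. The 10% and 20% rows have no source in the article.

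**6. Without replacement.** If 25 patients are treated and failures are dropped with no replacement and no rescaling of the cut-off, the number of successes does not change, and the chance of reaching 11 stays at 0.098. The Kaplan-Meier rate is still inflated.

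**The case against.** The strongest defence is that a 6-month evaluation was meant as *PFS status known at 6 months*, with an earlier death or progression counting as known. Three things favour this. The endpoint definition counts both as events. The analysis uses Kaplan-Meier with censoring, which would have little early work to do if everyone had to reach the landmark. And a 5% non-evaluable rate is hard to square with excluding every early failure. This may well be the intention, but no section says so. A statistician who applied the sentence as it stands would delete the deaths. The defence lowers certainty about what the sponsor meant; it does not repair the rule.

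Four stronger readings are tempting, and the article does not support them:

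- **All early progressors are dropped.** Durvalumab + tremelimumab combination therapy says that all patients are followed for progression and survival to 24 months after treatment ends. Treatment duration and criteria for retreatment foresees treatment through progression. Some early progressors may therefore have a landmark evaluation and count as events. Withdrawal and discontinuation criteria states continued RECIST follow-up after stopping study drug only for patients who have not progressed, so others may not. Only early deaths are certain to be lost.
- **Early leavers inflate PFS.** If leaving is unrelated to outcome, dropping them moves the estimate slightly down (0.484 against a true 0.50).
- **The type I error exceeds 10% in any case.** It rises only if excluded failures are replaced or the cut-off is applied to the evaluable number. The article states neither.
- **A patient stopped after tremelimumab but before durvalumab is excluded.** This depends on taking the dose condition to mean both drugs received; it may simply name the regimen.

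**Conclusion.** The point holds. As written, the population rule excludes patients who die before the landmark and any early progressors without a landmark evaluation, in conflict with the endpoint definition. Kaplan-Meier PFS and OS are biased upward, and this needs no assumption about replacement or cut-off. Read literally, OS at 6 months (12 months in the ovarian cohort) is 100% by construction.

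Confidence is high for the wording defect and low for its size. P0, P1, cohort sizes and the early-failure share are not given. The rise from 0.098 to 0.13, 0.18 or 0.32 illustrates one assumed design in which 5%, 10% or 20% of treated patients are excluded failures who are replaced; it is not an estimate for this trial. Because the rule governs the primary analysis, it should be corrected before any efficacy data are analysed.

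**What to change.** Replace the population sentence with a definition that does not depend on follow-up:

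- The efficacy population is all patients who started STEP 2 immunotherapy (at least one dose), whether or not a landmark evaluation exists.
- Progression or death before the landmark is an event.
- Patients lost without an event are censored at their last tumour assessment for PFS and at the last date known alive for OS.
- The set evaluated at 6 or 12 months, if kept, is a labelled sensitivity analysis only.
- The term *evaluable* in Sample size calculation is aligned with this definition.

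The ovarian landmark needs reconciling at the same time. Study endpoints and Analysis of efficacy endpoint(s) use 12 months, while Sample size calculation reads "except for ovarian cancer with an evaluation at 18 months given the results of olaparib in SOLO-2 trial". That is a separate inconsistency, but the new sentence has to name one time point.

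The cost is a short text change and no new data. The downside is that estimated PFS and OS may be lower than under the present rule.

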### Study objectives

The primary objective of the study is to evaluate the efficacy of olaparib + immunotherapy (durvalumab + tremelimumab) during 4 months, followed by durvalumab alone as maintenance treatment in patients with solid cancers and in response or stable, after prior molecular target therapy by olaparib based on molecular sequencing (mutation in homologous gene repair).

Study secondary objectives are:
To evaluate 6-month disease control rate (DCR) for all cohorts, except ovarian cohort which will be evaluated at 12-months.To evaluate 1 and 2-year PFS and overall survival (OS).To evaluate response rate after 6 weeks of olaparib therapy (STEP 1).To evaluate safety of molecular therapy by olaparib at the end of STEP1.To evaluate safety of molecular therapy (olaparib) + immunotherapy (durvalumab + tremelimumab) and immunotherapy in maintenance (durvalumab alone).

The study exploratory objective is to evaluate the immunogenic effect of olaparib (modification of immune infiltrate and immunogenic cell death markers on biopsy performed before and after olaparib treatment).

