### Study procedures

All patients respecting all eligibility criteria, namely presenting mutations in homologous repair genes will be included. Regimens sequence is presented in Fig. 1. Study will be divided into two successive steps:
*Step 1*After 6-weeks of olaparib, all patients from STEP 1 will have a CT scan.*Step 2*Depending on CT scan results, two situations will occur:
Patients with stable disease or partial response will follow olaparib + immunotherapy by durvalumab + tremelimumab during 4 months and then continue with durvalumab alone until progression or until 24 dosing maximum of durvalumab for all cohorts except for ovarian cohort with a maximum of 36 dosing.Patient with progression will be withdrawn from the study and treated according to standard care.

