### Treatment doses and regimens

#### Olaparib

Patients will be administered olaparib study treatment tablets orally at a dose of 300 mg bid.

The maximum duration of treatment with olaparib is 8 weeks, corresponding to the duration of STEP 1, + 4 months, the duration of the initial part of STEP 2. The initial dose of 300 mg bid will be made up of 2 × 150 mg tablets bid. All doses of study treatment should be taken at the same time every day approximately 12 h apart.

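### The analysis section times the STEP 1 olaparib response at 6 months instead of 6 weeks, and its only efficacy population leaves out patients who progressed at the STEP 1 scan

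*Protocol article*

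**What the plan says.** All references are to the protocol article.

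- **Endpoint.** Study endpoints lists, as secondary, "Response rate evaluated by CT scan, RECIST evaluation after 6 weeks of olaparib therapy". The Abstract and Study objectives give the same 6 weeks, and Study objectives ties it to STEP 1.
- **Analysis.** Analysis of efficacy endpoint(s) introduces a binomial confidence interval for disease control and continues: "The same method will be applied to describe the response rate after 6 months of olaparib in each cohort".
- **Population.** The same section opens with "Efficacy analyses will be performed in modified intent-to-treat population (ITT) population ie", defined as "all patients with a 6-month evaluation (12-month for ovarian cohort) and at least one dose of durvalumab + tremelimumab". Analyses are repeated in a per-protocol set of patients who received every planned dose. No other efficacy population is defined.
- **Patient flow.** Tables 1 and 2 admit to STEP 2 only patients who are responding or stable at the 6-week scan. For the rest, Study procedures states: "Patient with progression will be withdrawn from the study and treated according to standard care".
- **Olaparib exposure.** The Olaparib section says: "The maximum duration of treatment with olaparib is 8 weeks, corresponding to the duration of STEP 1, + 4 months".
- **Primary population.** Sample size calculation describes it as "evaluable patients who were in response or stable after 8 weeks of olaparib".

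**The concern.** There are two separate faults, and either would justify a correction.

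The first is timing. The endpoint is a 6-week reading on olaparib alone, while the analysis names 6 months. A patient assessed then would have had up to 4 months of the triple combination, so the result would not describe STEP 1.

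The second is the denominator, and it remains if 6 months is a slip for 6 weeks. A measure of response to STEP 1 would be computed only in patients who got through STEP 1, with the known failures removed.

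At stake is the trial's only estimate of olaparib activity before immunotherapy is added. In a non-randomised study, readers will use it as background when judging what the combination contributes.

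**Working it through.** **1. Can a 6-month olaparib response exist?**
Maximum exposure is 8 weeks plus 4 months. With 30.4375 days per month, 8 × 7 / 30.4375 = 1.84 months, and 1.84 + 4 = 5.84 months. This is below 6 months, and the last 4 months are combined with durvalumab and tremelimumab. No patient has 6 months of olaparib, and none has more than 8 weeks of it alone.

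**2. Reproducing the planned patient flow.**
Inputs: 270 included and 213 expected in STEP 2 (Study population and eligibility criteria); 80% expected stable or in response after 6 weeks (Sample size calculation).
- 270 × 0.80 = 216, against the stated 213.
- 213 / 0.80 = 266.25, rounded up to 267, against the stated 270.

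The figures agree to within 3%. So 270 − 216 = 54 to 270 − 213 = 57 patients (20% to 21%) are expected to leave after STEP 1. Without immunotherapy they cannot be in the modified ITT set or the per-protocol set.

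**3. Effect on a 6-week response rate.**
All responders are among those who move on, so the numerator is unchanged while the denominator shrinks. If responders and stable patients are equally likely to be evaluable later:

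reported rate / true rate = 1 / (share moving on) = 1 / 0.80 = 1.25, or 270 / 213 = 1.27 with the stated counts.

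The article gives no expected response rate, so the true rates below are assumptions.

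| Assumed true rate (of 270) | Responders | Rate on 216 | Rate on 213 |
|---|---|---|---|
| 10% | 27 | 12.5% | 12.7% |
| 20% | 54 | 25.0% | 25.4% |
| 30% | 81 | 37.5% | 38.0% |
| 40% | 108 | 50.0% | 50.7% |
| 50% | 135 | 62.5% | 63.4% |

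**4. Sensitivity.**
- Share moving on: at 70% the factor is 1 / 0.70 = 1.43; at 90% it is 1 / 0.90 = 1.11.
- Loss for lack of a later evaluation: if 5% are lost regardless of response, numerator and denominator both fall by 5% and the factor stays at 1.25.
- Differential loss: suppose a share f of responders, and no stable patients, is missing from the set. With true rate r, the inflation cancels when f = (1 − 0.80) / (1 − r). This gives 0.20 / 0.90 = 22% at r = 10% and 0.20 / 0.50 = 40% at r = 50%. So between 22% and 40% of responders would have to be lost, and no stable patients.

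**5. Six weeks against eight.**
Tables 1 and 2 and Study procedures gate STEP 2 on a scan after 6 weeks. Sample size calculation selects the primary population by status after 8 weeks, and the Olaparib section gives 8 weeks as the length of STEP 1. A maximum treatment duration can run past the scan date without contradiction; selecting the population by status at 8 weeks does not match the gate.

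**The case against.** The strongest reply is that 6 months is a slip. Every other mention of this assessment says 6 weeks, and the olaparib cap makes the literal version impossible. That is probably right, but it settles only the timing fault.

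On the population, the modified ITT definition is evidently written for STEP 2 endpoints, and no sentence applies it to STEP 1 response by name. A fuller document might hold a separate STEP 1 set. This has some force. Even so, the opening sentence covers efficacy analyses without exception, and the olaparib response sentence follows under it. This is a stated rule that does not suit the endpoint, not a detail left out.

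It is also fair to say that this is a descriptive secondary rate. The primary endpoint is PFS timed from the first immunotherapy dose, and STEP 1 response does not enter that test.

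A reader might infer more than the article supports:
- **That the rate will be both inflated and mixed with the combination.** These belong to alternative readings. The 1.25 factor applies to a 6-week response on the modified ITT set. A true 6-month reading would mix in the combination and later progressions, and could err either way.
- **That the 80% planning assumption could never be checked.** Scan results and the counts entering each step check it whatever the efficacy denominator.
- **That disease control would read 100%.** Disease control after STEP 1 is not an endpoint; it is defined from the start of immunotherapy.
- **That everyone who progresses on olaparib is excluded.** Only progression at the STEP 1 scan bars STEP 2; progression during the combination does not in itself remove a patient.
- **That requiring a 6-month evaluation inflates the rate further.** The direction depends on who lacks that evaluation, which the article does not tell us.

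**Conclusion.** The point holds in two parts. The analysis sentence contradicts the 6-week endpoint and names a quantity that cannot be observed as an olaparib-alone effect. Independently, the stated efficacy population removes STEP 1 progressors, which inflates a 6-week response rate by about 1.25 to 1.27 at the planned 80% moving on (1.43 at 70%, 1.11 at 90%).

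The size rests on that planning value and on similar later evaluability of responders and stable patients. The absolute rates shown rest on assumed true response rates. The correction should be made, but it concerns a secondary descriptive endpoint and leaves the primary test untouched. The 8-week wording is a related but separate inconsistency in how the primary population is described.

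**What to change.** 1. In Analysis of efficacy endpoint(s), replace the 6-month wording with the 6-week STEP 1 CT assessment already defined in Study endpoints.
2. Name a population for it: all patients who took at least one dose of olaparib, with progressors and patients with a missing or unevaluable scan kept in the denominator as non-responders. Limit the modified ITT and per-protocol sets to the STEP 2 efficacy endpoints.
3. Reconcile the 8-week statements in Sample size calculation and the Olaparib section with the 6-week scan that gates STEP 2, so that the primary population is defined by the assessment that actually admits patients. Which STEP 1 duration is intended is for the sponsor to state.

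The cost is a few sentences. The scan is already required of every STEP 1 patient, so no new data are needed. A 6-week response rate will be lower than on the modified ITT set, by a factor of about 0.79 to 0.80 (213/270 to 216/270) under the planning assumptions.
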